#### Analyses of Weekly trajectories

To investigate the trajectories of weekly variables over the intervention period (H6a, H6b, H6c), we will use growth models in a multilevel modelling framework. Two models will be tested for burnout and vigor respectively. They will contain a random intercept and a random linear slope for the occasion of measurement at the subject level. This random slope for occasion measurements will allow each participants’ growth trajectory over time to be estimated. A linear and quadratic effect of occasion measurements will be added as fixed effects to examine the linear and accelerated evolution of the outcomes over time. The three orthogonal contrasts will be added as fixed factors to the model, as well as their interaction terms with “time” and “time2”. Thus, we will examine if there is an effect of the intervention (H6a), the type of activity or need-supportive style (H6b) on the level of and rate of change in burnout and vigor over time. In all analyses we will control for variables that could influence participants’ outcomes, such as weekly needs satisfaction-frustration at work and weekly workload.

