### Weekly trajectories of employee burnout, vigor, and psychological recovery mechanisms

Following the recommendations by de Vries and colleagues [29, 66], we will examine the employees’ well-being and recovery trajectories during the course of the trial in order to answer two questions: (a) what is the minimum exposure to exercise or Theatre condition required for burnout and vigor to differ between interventions and control conditions? and (b) are the feeling of having recovered and the experiences of recovery among participants in PA and Theatre condition related to differences in their vigor and burnout trajectories? To be able to answer these questions and provide a finer grain of analysis on the development of well-being indicators during the intervention and on the relationships between these indicators and the recovery mechanisms, during each week of the intervention we will assess the primary outcomes (burnout, vigor) and the psychological mechanisms of recovery (detachment, relaxation, mastery, control, relatedness, and positive affects experiences) using single-item scales. While it is difficult to predict precisely when the well-being indicators will change as a function of the intervention, we nevertheless expect that:*Hypothesis 6a:* Participants in the PA and Theatre conditions report a decrease in feelings of burnout and/or an increase in vigor each week over the intervention period compared to participants in the control condition.*Hypothesis 6b:* Participants in the PA-need-supportive style conditions report a decrease in feeling of burnout and/or an increase in vigor each week over the intervention period compared to participants in the PA-traditional style and Theatre conditions.

Regarding the relationships between recovery and burnout/vigor trajectories, we expect that:*Hypothesis 6c:* Participants in intervention groups who experience greater feelings of psychological detachment from work, relaxation, mastery, control, relatedness, or positive affects experiences during the sessions, show a larger improvement in their weekly burnout and/or vigor trajectories compared to participants who experience lower feelings during these sessions.

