### Measures

Table 1 provides an overview of the measurement points of the primary and secondary outcomes, mediators, moderators and control variables, and manipulation check variables. At the end of the second session of each week, participants will complete a questionnaire measuring their weekly burnout, vigor, needs satisfaction at work and workload, as well as recovery mechanisms experienced, affects and effort perception during sessions (only for the 3 intervention groups). Five minutes are requested to complete the questionnaire. In week six of the program, participants will complete an online survey measuring job characteristics, and intervention groups will wear a 3-axis accelerometer to assess their energy expenditure during PA or theatre sessions. In week eight of the intervention, all instructors will be recorded audio-visually and participants will complete an online survey assessing their instructor’s motivational style during the sessions. At the beginning of the final session of the intervention participants will replicate the cardiorespiratory fitness test, and at the end of the intervention, participants will complete an online survey measuring the same variables as those assessed at baseline. Finally, three and six months after the end of the intervention, participants will be invited to complete the follow-up online questionnaire. In order to measure the *compliance* to the program, instructors from the three intervention groups will be asked to indicate the participants’ presence or absence at each session in a register.

**Table 1 Tab1:** Overview of the measurement points for the primary and secondary outcomes, during intervention and weekly measures, and follow-up measurements

	Variables	Pre-intervention (T0)	During intervention (T6 or T8)	Weekly (T1-T10)	Post-intervention (T11)	Follow-up at 3 and 6 months (T12–13)
Primary outcomes	− Burnout	✓		✓	✓	✓^a^
	− Vigor	✓		✓	✓	✓^a^
Secondary outcomes	− Job satisfaction	✓			✓	✓^a^
	− Work motivation	✓			✓	✓^a^
	− Work performance	✓			✓	✓^a^
	− Work ability	✓			✓	✓^a^
Psychological and physiological mediators	− Off-job recovery activities	✓			✓	
	− Psychological detachment	✓		✓^a^	✓	
	− Relaxation	✓		✓^a^	✓	
	− Control	✓		✓^a^	✓	
	− Mastery	✓		✓^a^	✓	
	− Relatedness	✓		✓^a^	✓	
	− Positive Affects			✓^a^		
	− Cardiorespiratory Fitness	✓			✓	
Moderator variable	− Compliance to activity sessions			✓^a^		
Control variables	− Job characteristics	✓	✓(T6)	✓^b^	✓	

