##### Work-related variables

Employees will be asked to complete a ten-item questionnaire after the second session each week, to assess their weekly *burnout at work* (i.e., three single-items from the SMBM; see above), *vigor at work* (i.e., three single-items from the SMVM; see above), *basic need satisfaction* versus *frustration at work* (i.e., three single-items from the Needs Satisfaction-Frustration at Work Scale; see above), and *workload* (one single-item “How heavy was your workload today?” used by Thøgersen-Ntoumanis et al., [28]). Scores will be rated using a bipolar visual analogue scale of ten centimeters with two opposing anchors (e.g., “never” vs. “always”; “very light” vs. “very heavy”).

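### The weekly growth models name no pre-intervention score and allow only linear and quadratic time, so the level contrasts lose precision and the week of onset depends partly on the curve

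*Protocol article*

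**What the plan says.** The section on weekly trajectories in the Background sets question (a): "what is the minimum exposure to exercise or Theatre condition required for burnout and vigor to differ" between the activity and control conditions. The Measures section fixes when the data arise: "At the end of the second session of each week, participants will complete a questionnaire measuring their weekly burnout, vigor". T1 therefore follows two sessions in the three activity arms. Under Work-related variables the weekly format is given: "Scores will be rated using a bipolar visual analogue scale of ten centimeters". At T0 the full SMBM and SMVM are answered on a seven-point Likert scale.

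Under Analyses of Weekly trajectories the model is set out:

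- data: "To investigate the trajectories of weekly variables over the intervention period (H6a, H6b, H6c), we will use growth models";
- time: "A linear and quadratic effect of occasion measurements will be added as fixed effects", with a random intercept and a random linear slope;
- arms: "The three orthogonal contrasts will be added as fixed factors to the model, as well as their interaction terms" with time and time squared;
- reading: effects "on the level of and rate of change in burnout and vigor over time";
- controls: variables "such as weekly needs satisfaction-frustration at work and weekly workload".

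T0 burnout or vigor is named neither as an occasion nor as a covariate in this section. The mediation models do control for baseline, and the pre-post models include the pre score as a time point.

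**The concern.** Two things follow from a series that starts after treatment has begun and has no earlier anchor.

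First, the level contrast at the start of the series combines whatever difference randomisation left between arms with any effect of the first two sessions. A benefit complete by T1 and constant afterwards appears only as a level difference, with zero slope and zero curvature. A starting difference gives the same pattern. The T0 score would help to separate the two and would reduce unexplained variance, but it is not named.

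Second, question (a) asks when the arms begin to differ, while the model returns a level, a slope and a curvature. A polynomial of degree two spreads a late or abrupt change over the weeks before it. An onset week read from the fitted curve is then partly a product of the chosen shape.

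**Working it through.** The plan gives no figure of its own for the weekly analysis. The inputs are 35 per group and d = 0.35 (Sample size), ten weekly occasions (Table 1), and the model terms above. The correlation r between the T0 score and weekly scores is not in the document; I assume 0.4 to 0.6.

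**Chance T0 imbalance, in SD units, 35 per arm**

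- Waiting list against the other three: √(1/105 + 1/35) = 0.195; 95% range ±1.96 × 0.195 = ±0.38.
- PA-TS against PA-NSS: √(2/35) = 0.239; 95% range ±0.47.

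Only r times an imbalance carries into the weekly level:

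| Contrast | Raw 95% range | Carried, r = 0.4 | Carried, r = 0.6 |
|---|---|---|---|
| Waiting list vs other three | ±0.38 | ±0.15 | ±0.23 |
| PA-TS vs PA-NSS | ±0.47 | ±0.19 | ±0.28 |

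**Error rate of the level test**

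Given an imbalance of k standard errors and no true effect, the test statistic has mean r·k and variance 1 − r². At r = 0.5 and nominal 0.05, the rejection rate is 0.024 for k = 0, 0.048 for k = 1 and 0.134 for k = 2. Averaged over all randomisations it is 0.050.

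**Precision**

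Adjusting for T0 multiplies the standard error by √(1 − r²).

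- r = 0.4: √0.84 = 0.917, a cut of 8%.
- r = 0.6: √0.64 = 0.80, a cut of 20%.

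**Fitting a delayed onset**

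Let the true arm difference be 0 in weeks 1 to 5 and 1 in weeks 6 to 10. This pattern is antisymmetric about 5.5, so the fitted quadratic coefficient is zero. The slope is (0.5 + 1.5 + 2.5 + 3.5 + 4.5)/82.5 = 12.5/82.5 = 0.1515, and the fit is 0.5 + 0.1515 × (week − 5.5).

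| Week | True | Fitted |
|---|---|---|
| 3 | 0 | 0.12 |
| 4 | 0 | 0.27 |
| 5 | 0 | 0.42 |
| 6 | 1 | 0.58 |

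A step that does use the curvature behaves in the same way. A difference of −0.35 starting at week 5 is fitted as −0.09 at week 3, −0.17 at week 4 and −0.23 at week 5. The curve shows a difference before one exists and understates it when it begins. With week as a factor, the expected difference before onset is 0.

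**The case against.** The strongest reply is that randomisation already handles imbalance: it is part of the standard error of the level contrast, and the overall error rate is nominal. That stands. The 0.134 applies only after a 2-SE imbalance and is offset by rates below 0.05 when arms happen to be balanced.

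H6a and H6b are worded as change over the weeks. The contrast-by-time terms test them, and a constant starting difference leaves those terms unmoved. That also stands, although the plan says it will read the level as well.

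The control list is given by example, so T0 is unnamed rather than ruled out, and an article may leave its covariate list to a fuller document. This stands for the covariate and lowers its weight. It does not cover the form of time, which the article fixes, or the mismatch between that form and question (a).

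A quadratic is a conventional summary of ten occasions, the protocol admits that timing is hard to predict, and nothing in it points to a step. This is fair: the step is an illustration, not a forecast. But uncertainty about timing is itself a reason not to answer a timing question from a preset shape alone.

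A reader might also infer that T0 can have no place in the series because the response formats differ. That goes too far, since the weekly items are drawn from the T0 questionnaires. The difference does make T0 more natural as a covariate than as an extra occasion.

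**Conclusion.** The point holds in a limited form. The level contrasts are valid but less precise than they could be: T0 adjustment would cut their standard error by 8 to 20% at an assumed correlation of 0.4 to 0.6. Without an anchor, an effect already present at T1 cannot be told from a chance starting difference. The minimum-exposure question would be answered partly by the imposed curve; in the week-6 step, 27% and 42% of the effect is displayed one to two weeks before it exists.

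Two stronger readings are not supported. One is that chance imbalance invalidates the level test or produces excess false positives; over randomisations it does not. The other is that the imbalance is as large as the planned effect. The raw ranges of ±0.38 and ±0.47 exceed 0.35, but the part that a T0 covariate could explain is r times those, ±0.15 to ±0.28, and d = 0.35 was planned for change rather than for a weekly level. The pre-post primary analysis is untouched.

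**What to change.** Name the T0 SMBM total as a covariate in the weekly burnout models and the T0 SMVM total in the weekly vigor models, including the moderator models built on them.

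Keep the growth model for H6a and H6b. For question (a), also refit with week as a 10-level factor. Report the baseline-adjusted difference of each activity arm from the waiting list at every week, with a confidence interval, as a descriptive estimate of onset and a check on the quadratic.

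Minimum exposure should not be defined as the first week from which simultaneous intervals exclude zero through T10. With 35 per arm, a between-week correlation of 0.5 (assumed) and a critical value of about 2.7, an unadjusted difference would have to exceed about 2.7 × 0.239 = 0.65 SD. At a true 0.35 such a rule would rarely give an answer, and the answer would depend on sample size.

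The T0 scores are already collected, so only the analysis wording changes. The cost is wider week-specific intervals than the smoothed curve gives: at r = 0.5 and full retention, about ±1.96 × 0.239 × √0.75 = ±0.41 SD. The onset estimate will therefore be rough and should be reported as such.

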#### Analyses of Moderators

To examine whether participants’ experiences (i.e., detachment from work, relaxation, mastery, control, relatedness, or positive affects) during sessions moderate their well-being trajectories (H6c), a model comparable to the aforementioned models will be tested, except that the six experiences will be added as between-factors to the model and will also be modeled to interact with time (i.e., cross-level interaction). In these analyses, we will use each individual’s mean scores of the experiences during the 10 weeks of the intervention. Such a model, already used previously [66] will test if participants’ rate of change in well-being over time varies as a function of their average recovery experiences during the Nordic walking/ Theater sessions. To test if participants’ compliance to the intervention moderates their well-being trajectories (H7), we will also use a multilevel modelling framework. Two models will be tested for burnout and vigor respectively. This model is equivalent to the model testing weekly trajectories (see above), except that “compliance” will be added as a fixed factor in the model and will interact with other terms. This analysis strategy testing the moderation effect of compliance has been used in a study with a similar protocol design [66].

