**Methods:**

Employees of the authors’ University (*N* = 140) will be recruited via email, leaflets, and posters. Participants will be randomized to one of the four arms of the trial: (1) Physical Activity Traditional Style, (2) Physical Activity Need-Supportive Style, (3) Theatre condition, and (4) Waiting List Control. The experimental phase will last 10 weeks, followed by a six-month follow-up. During the ten weeks of the intervention, all groups – except the waiting list control – will carry out two activity sessions per week. Primary outcomes are burnout and vigor, secondary outcomes are work motivation, job satisfaction, work performance and work ability. These variables will be assessed before and after the intervention, and at three and six months after the end of the intervention. Moreover, burnout, vigor, needs satisfaction at work and psychological mediators will be assessed weekly throughout the intervention period.

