In view of this background, the aim of the present study is threefold. Firstly, to test the effects of a workplace PA intervention on work-related burnout and vigor using a design that allows for strong causal inferences and rules out alternative explanations. Specifically, the objective is to examine if a 10-week PA program including two Nordic walking sessions per week could reduce burnout and improve vigor at work among employees with moderate-to-high levels of burnout who do not participate in sport regularly, in comparison with another attractive leisure activity – i.e., Theatre condition – or a waiting list control condition. The second objective is to capture the effect of the instructor’s motivational style when supervising PA, by testing if a psychological needs supportive motivational style increases the benefits of PA on burnout and vigor at work, compared to a traditional motivational style. The third objective is to investigate the mediators of the relation between PA and burnout/vigor at within- and between-subject levels, in order to improve knowledge on the mechanisms explaining the effect of PA on well-being at work.

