	− Needs satisfaction at work	✓	✓(T6)	✓	✓	
	− Workload at work			✓		
Manipulation check	− Instructors observed motivating style		✓(T8)			
	− *participants’ perception of the instructor’s motivating style*		✓(T8)			
	− Objective effort during sessions		✓(T6)			
	− Perceived effort during sessions			✓^a^		

^a^Variables only collected in intervention groups; ^b^Variables only collected in the waiting-list group

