
#### Analyses of Psychological and Physiological Mechanisms of the PA – Burnout/Vigor Relationship

Multiple mediation modelling will be used to examine the hypotheses that psychological (i.e., detachment, relaxation, mastery, control, relatedness, and positive affects experiences) and physiological (i.e., cardiorespiratory fitness) mechanisms partially or fully mediate the relationships between workplace PA or expressive activity on one hand and burnout and vigor on the other (H5). Two separate models will be generated with burnout and vigor as dependent variables. To handle the categorical independent variable (i.e., the experimental conditions), we will follow Hayes and Preacher’s [95] guidelines for calculating direct and indirect effects using a multicategorical predictor. Specifically, contrast coding will be used to examine the relative effect of workplace intervention (versus WLC), PA (versus Theatre condition) and PA with instructor using a need-supportive style (versus PA-TS) (see above). The scores of the mediating and dependent variables will be analyzed while controlling for the levels of measurement at baseline (i.e., the autoregressive effects). Autoregression allows the value of the variable at a previous time point to be statistical controlled, thereby reducing the likelihood of bias [96]. Bootstrapping procedures will be used to test the statistical significance of indirect effects of the proposed mediating variables [97]. Bootstrapping is a nonparametric resampling procedure for estimating indirect effects using adjusted (asymmetric) confidence intervals. This procedure is very useful in cases of multiple mediations, for which it is interesting to determine not only whether an indirect effect exists, but which mediator(s) contribute(s) significantly to the effect while controlling for other potential mediators. Point estimates and confidence intervals of relative indirect effects (total and specific) will be estimated from 5000 bootstrapped samples and 95% bias-corrected confidence intervals.

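### The third objective promises mediators at the within-subject level, but no described analysis estimates a within-person relation; the weekly recovery experiences enter only as 10-week person means

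*Protocol article*

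**What the plan says.** - **Aim.** The Background (Physical activity and burnout/vigor at work) states: "The third objective is to investigate the mediators of the relation between PA and burnout/vigor at within- and between-subject levels".
- **Data.** The abstract says that "burnout, vigor, needs satisfaction at work and psychological mediators will be assessed weekly throughout the intervention period". In Table 1 the weekly detachment, relaxation, control, mastery, relatedness and positive affect scores carry the footnote "Variables only collected in intervention groups". The waiting list arm therefore supplies weekly burnout and vigor but no weekly experiences.
- **Mediation (H5).** In the analysis section on psychological and physiological mechanisms, "Multiple mediation modelling will be used to examine the hypotheses". The predictor is experimental condition, coded by contrasts. Mediator and outcome scores are adjusted for baseline, and indirect effects are bootstrapped.
- **Weekly trajectories (H6a, H6b).** Growth models with time, contrasts and their interactions. The weekly covariates named are needs satisfaction-frustration and workload.
- **Experiences and trajectories (H6c).** In Analyses of Moderators, "the six experiences will be added as between-factors to the model and will also be modeled to interact with time", and for this "we will use each individual’s mean scores of the experiences during the 10 weeks of the intervention". The stated test is whether participants' "rate of change in well-being over time varies as a function of their average recovery experiences".

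**The concern.** The within-subject question is whether a participant has lower burnout or higher vigor in, or after, weeks with more detachment, relaxation and so on than is usual for that person. That is a different quantity from whether people with higher average experiences improve faster; the two can differ in size or in sign, and one cannot stand in for the other. The trial collects the weekly scores that could address the first question, but the analysis it fixes for them addresses only the second.

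There is also a question of order. The mean runs over weeks 1 to 10, and so does the trajectory. Experiences reported in week 10 thus help to explain change that took place in weeks 1 to 9. Participants who are already improving may rate their sessions more favourably, and the person mean cannot separate that from the reverse.

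At stake is the within-subject half of a stated objective, and how far an H6c result can be read as evidence of mechanism. The comparisons on the primary outcomes are not affected.

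**Working it through.** The plan gives no figure to reproduce here. The check follows the third objective through each described analysis, and then illustrates two properties of the person-mean term.

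**1. Which analysis could give a within-person result?**

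| Analysis | Predictor of interest | Varies within a person? |
|---|---|---|
| H5 mediation | Condition; baseline-adjusted mediator scores | Condition is fixed per person; no repeated weekly mediator is described |
| H6a, H6b growth models | Time, contrasts; weekly needs satisfaction and workload as covariates | Time and covariates do, but no recovery experience is named |
| H6c growth models | 10-week mean of each experience, and mean by time | The mean does not |
| H7 models | Compliance, in place of experiences | No recovery experience is used |

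None contains a recovery experience that varies from week to week.

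**2. How much is averaged away?** Sample size section: 35 per group, 25% dropout; 35 × 0.75 = 26.25, about 26. Three activity arms and ten weeks give:

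- 3 × 26 × 10 = 780 to 3 × 35 × 10 = 1,050 person-weeks, reduced to 3 × 26 = 78 to 3 × 35 = 105 means.
- With a one-week lag, 3 × 26 × 9 = 702 to 3 × 35 × 9 = 945 pairs.

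These are ceilings. They assume a completed booklet every week, and missed sessions lower them. Only the predictor is averaged; weekly burnout and vigor are kept.

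**3. Does the person-mean term respond to a within-person effect?** An experience score is the sum of the person mean and the weekly deviation, and the deviations sum to zero for each person, so the mean carries no within-person variation. As an illustration, 1,000 simulated trials were run under assumed parameters: 105 people, ten weeks, SD 1 for both person means and weekly deviations, residual SD 0.7, and a true person mean by time coefficient of −0.03. Each person's fitted slope was regressed on that person's mean.

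| True weekly effect | Person mean by time estimate | Estimate from weekly deviation |
|---|---|---|
| −0.5 | −0.030 | −0.50 |
| 0 | −0.030 | 0.00 |
| +0.5 | −0.031 | +0.50 |

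The planned coefficient is the same whatever the within-person effect. The weekly deviation recovers it.

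**4. Can reverse influence alone produce an H6c association?** In a second assumed scenario (105 people, individual slopes with SD 0.1), each unit of the previous week's outcome lowered the experience score by 0.5, and experience had no effect on the outcome. The person mean by time test was significant at 5% in 37% of 1,000 runs. The rate belongs to these assumptions and is not a forecast for this trial. It shows only that the association does not establish order.

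**The case against.** The strongest reply has five parts.

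- **The person mean fits its own hypothesis.** H6c compares participants with higher and lower experiences, and the section on moderators does not claim to deliver mediation. This stands. A reader might infer that the person mean is the wrong predictor for H6c; the wording of H6c does not support that.
- **A condensed article may leave a further model to the full plan.** No hypothesis from H1 to H7 states a week-to-week effect, and the within-subject phrase might mean no more than individual change. This stands only in part. The article does not leave the handling of the weekly experiences open. It fixes them as person means entered between persons, and that conflicts with an aim naming both levels for the mediators themselves. Random slopes for burnout and vigor describe change in the outcome, not its relation to a mediator.
- **Other weekly data may enter the mediation model.** Table 1 lists positive affects only as a weekly measure, yet H5 includes them as a mediator. True, but how they enter is not stated, and the model described compares persons.
- **Reverse influence is a risk for any experience measured after randomization, and the plan claims association only.** This stands. One might infer that H6c is invalid or that its result will be reverse causation; the documents support neither.
- **A within-person slope is not mediation.** Condition is fixed per person, and the waiting list arm has no weekly experiences. This stands and limits what the remedy may be called.

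**Conclusion.** The concern holds in a limited form. Followed as written, the plan yields no within-person estimate for any recovery experience, although the third objective names that level and the experiences are measured weekly in three arms. H6c is suitably specified for the between-person question it asks, but its result is an association over one shared period and cannot show that experience preceded improvement.

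A reader might go further and conclude that the trial cannot address the within-subject question. The documents do not support that: the weekly scores are collected, and the gap lies in the analysis described. Nor would a within-person term complete the mediation argument, since it relates experience to outcome in the activity arms and says nothing about how the intervention effect against the waiting list arises.

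The size is up to 780 to 1,050 person-weeks of experience data reduced to 78 to 105 means, with one half of a secondary, mechanistic objective left without an analysis. This rests on reading the within-subject level as a week-to-week relation between experience and outcome, and on the article stating the planned handling of the weekly experiences in full. The plan should be changed, but the primary conclusions do not depend on it.

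**What to change.** - Keep the person mean by time term as the test of H6c, and state that its result is associational.
- In the same growth models, for the three activity arms, add each experience's weekly deviation from the person mean. Report the same-week coefficient and a version using the previous week's deviation.
- Label these as within-person associations between experience and burnout or vigor in the activity arms. Do not present them as mediation of the intervention effect or as a contrast with the waiting list.
- If this is not wanted, remove the within-subject level from the third objective.

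The cost is analysis wording and more model terms: with six experiences, six added deviation terms in each burnout and vigor model, in the same-week or the lagged form. The lagged version loses one week of ten. The lag reduces reverse influence without removing it, partly because the person mean from which the deviation is taken still includes later weeks. No new data are needed.

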### Moderator effects of compliance

We will also investigate the effect of participants’ compliance to the program on burnout/vigor. Compliance refers to the frequency with which the participants attend the activity sessions during the length of the program. Studies [37] had shown that the most assiduous participants benefit more from the effects of the intervention and report higher work-related well-being at the end of the intervention, compared to less assiduous participants. Therefore, we hypothesize that:*Hypothesis 7:* The positive effect of PA on burnout and/or vigor will be more pronounced among participants with higher compliance to activity sessions compared to participants with lower compliance.

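### The H7 compliance model cannot separate an effect of attending from attendance that responds to burnout, so it should be reported as associational and not as a test of H7

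*Protocol article*

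**What the plan says.** The Protocol article, under Moderator effects of compliance, defines the variable: "Compliance refers to the frequency with which the participants attend the activity sessions during the length of the program". It cites studies in which the "most assiduous participants benefit more from the effects of the intervention", and then states H7: "The positive effect of PA on burnout and/or vigor will be more pronounced among participants with higher compliance to activity sessions", relative to those with lower compliance.

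Under Measures, "instructors from the three intervention groups will be asked to indicate the participants’ presence or absence at each session in a register". Table 1 marks compliance with the footnote "Variables only collected in intervention groups". In the activity arms the weekly burnout and vigor ratings are filled in on paper when the second session of the week ends; the waiting list answers online.

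Under Analyses of Moderators, the H7 model is the weekly trajectory model with one change: compliance "will be added as a fixed factor in the model and will interact with other terms". The trajectory model covers the ten intervention weeks. It adjusts for weekly need satisfaction and workload, given as examples. Neither section names earlier burnout or vigor as an adjuster. The justification for the H7 model is that a similar study used it, and Strengths and Limitations does not mention the issue.

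**The concern.** Attendance happens after randomization and may be a consequence of the outcome it is used to explain. If total attendance is the exposure, sessions in weeks 6-10 help to explain burnout in weeks 1-5. An employee whose burnout is rising may come less often. Total attendance is then lower in people with worsening slopes, and the model shows better trajectories in better attenders. That is the pattern H7 predicts, and it needs no benefit from attending.

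The waiting list gives no help, because it has no attendance values. At a given level of attendance there is no randomized comparison, so a larger effect of PA in good attenders cannot be told apart from people who are doing better attending more. At stake is whether the trial may report that attendance strengthens the effect, which readers may take as a dose-response finding.

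**Working it through.** **Inputs from the Protocol article.** 35 participants per group (Sample size), so 3 × 35 = 105 in the activity arms; ten weekly ratings; twenty sessions, two per week. The article gives no figure for H7, so there is none to reproduce.

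**Assumed inputs, first set.** Burnout y has between-person SD 0.7 and within-person SD 0.6. Individual slopes have SD 0.05 or 0.08 per week, that is 9 × 0.05 = 0.45 or 9 × 0.08 = 0.72 points over the nine weekly steps. The model is

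y(i,w) = a(i) + b(i) × w + e(i,w), with no attendance term, so the null is true;

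logit P(attend in week w) = 1.1 − ln(OR) × y(i,w−1).

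At average burnout, attendance is 1/(1 + e^−1.1) = 0.75. The OR is the factor by which one more point of burnout lowers the odds of attending the next week. Each person's slope is regressed on the fraction of sessions attended, a two-stage approximation to the compliance-by-time term. Nominal error in the H7 direction is 2.5%.

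**Intermittent non-attendance, all weeks observed (1,000 trials per setting).**

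| OR | False positives in the H7 direction, slope SD 0.05 to 0.08 |
|---|---|
| 1 | 2.1-2.7% |
| 1.25 | 5.9-19.6% |
| 1.5 | 12-42% |
| 2 | 16-65% |

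Over repeated runs of this set-up, ORs of 1.25-2 gave about 5-18% at slope SD 0.05 and 14-71% at 0.08. A fitted mixed model at slope SD 0.05, with quadratic time, random intercept and slope, and extra attendance variation unrelated to burnout, gave 6-8% (120 trials per setting).

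**Permanent stopping, same parameters.** 2-8% with all weeks observed; 5-48% when ratings end with attendance.

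**Second set of assumptions.** Intercept SD 1, weekly error SD 0.6, SD of the individual nine-week change 0.5 or 1.0, 105 participants, two-sided 5% test, 400 runs per setting. Entries are rejections in the H7 direction for log-odds of 0.5 and 1.0 per SD of burnout.

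| Attendance depends on | Change SD 0.5 | Change SD 1.0 |
|---|---|---|
| Baseline burnout only, all weeks observed | 2.2%, 2.2% | 3.0%, 3.3% |
| Last week's burnout, intermittent, all weeks observed | 7.7%, 13.3% | 59.0%, 72.3% |
| Last week's burnout, permanent stopping, all weeks observed | 3.3%, 1.5% | 5.2%, 8.7% |
| Same stopping, ratings only while attending | 16.3%, 48.5% | 27.3%, 75.2% |

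Both sets agree. The bias needs attendance to follow changing burnout. Stopping matters mainly when ratings are lost as well.

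**Two candidate remedies.** (a) Instrumental estimate: effect per session = (T11 difference, PA minus waiting list, adjusted for T0) ÷ (mean sessions attended in PA − 0). At 75% attendance the divisor would be 0.75 × 20 = 15, so this is the intention-to-treat effect rescaled. With a simulated PA effect of 0.6, identical for everyone whatever their attendance, it was significant in 94% of trials and agreed with the intention-to-treat test in all of them. It does not test moderation. (b) Attendance up to the previous week, with the prior and baseline ratings in the model: still falsely significant in 23-96% under intermittent non-attendance, because stable differences between persons remain.

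**The case against.** **Coding.** The article does not say how compliance is coded. Table 1 lists it as weekly, and the trajectory section also uses the term fixed factor for ordinary fixed effects. This stands as a caution. The definition over the length of the programme, and the contrast of higher with lower compliers, make total attendance the likelier reading. Coding it as past attendance would not by itself remove the problem, as remedy (b) shows.

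**Planned adjustment.** Weekly workload and need satisfaction are controlled. That addresses the overloaded employee who stays away, but not feedback from burnout itself.

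**Size and direction.** The slope SDs and odds ratios are assumptions. Attendance driven only by baseline burnout leaves the interaction test near nominal, and people who stop because they feel better would push it the other way. All of this stands.

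**Stronger readings.** A reader might infer that people who quit because they feel worse are enough to confirm H7. With all weeks observed they are not: the rates were 2-8%. The higher rates need lost ratings as well. That is likely, since activity-arm ratings are taken at the session, but the article does not say what happens to an absentee's questionnaire. A reader might also cite a compliance main effect, falsely significant in about 90% or more of simulated trials. That is not H7, which is tested as moderation of trajectories, and the figure is upper-end because attendance was driven only by burnout and chance. Nor is the main intention-to-treat comparison affected, since it does not use compliance.

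**Conclusion.** The point holds. The article fixes a specific model for H7, and that model cannot identify what H7 claims. This is not a detail that can be left to a fuller plan.

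Under a true null, false support for H7 was about 5-18% at slope SD 0.05 and 14-71% at 0.08 when attendance responds to the previous week's burnout. With permanent stopping it was 2-8%, or 5-48% if ratings are also lost. These figures rest on assumed parameters, on total attendance as the coding and mostly on a two-stage approximation, so they show that the error can be large, not how large it will be in this trial. Whichever way attendance responds to changing burnout, the compliance term is not an effect of attending. The consequence is limited to H7 and to any dose-response claim drawn from it.

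**What to change.** In Analyses of Moderators, state that the compliance model is descriptive and associational, and that a significant compliance term will not be reported as confirming H7 or as a dose-response effect of PA.

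If an effect of attending is wanted, add it as a separate estimate and not as a test of H7: the effect of sessions attended on the T11 score, with allocation (PA versus waiting list, whose attendance is zero) as instrument and the T0 score as covariate. Say that it is the intention-to-treat effect rescaled by attendance, and that it assumes allocation acts only through attending. T11 is an online survey, so this outcome does not depend on being at a session. A lagged-attendance weekly model adjusted only for the prior rating should not replace it.

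The cost is a change of wording and, optionally, one model on data already planned. H7 loses its confirmatory claim, and the added estimate has a wider interval.
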